## Abstract

Recent studies indicate that the interplay between diet, intestinal microbiota composition, and intestinal permeability can impact mental health. More than 10% of children and adolescents in Iceland suffer from mental disorders, and rates of psychotropics use are very high. The aim of this novel observational longitudinal case-control study, “Meals, Microbiota and Mental Health in Children and Adolescents (MMM-Study)” is to contribute to the promotion of treatment options for children and adolescents diagnosed with mental disorders through identification of patterns that may affect the symptoms. *All* children and adolescents, 5–15 years referred to the outpatient clinic of the Child and Adolescent Psychiatry Department at The National University Hospital in Reykjavik, Iceland, for one year (*n≈1*50) will be invited to participate. There are two control groups, i.e., sex-matched children from the same postal area (*n≈1*50) and same parent siblings (full siblings) in the same household close in age +/- 3 years (*n*<150). A three-day food diary, rating scales for mental health, and multiple questionnaires will be completed. Biosamples (fecal-, urine-, saliva-, blood samples, and buccal swab) will be collected and used for 16S rRNA gene amplicon sequencing of the oral and gut microbiome, measurements of serum factors, quantification of urine metabolites and host genotype, respectively. For longitudinal follow-up, data collection will be repeated after three years in the same groups. Integrative analysis of diet, gut microbiota, intestinal permeability, serum metabolites, and mental health will be conducted applying bioinformatics and systems biology approaches. Extensive population-based data of this quality has not been collected before, with collection repeated in three years’ time, contributing to the high scientific value. The MMM-study follows the “Strengthening the Reporting of Observational Studies in Epidemiology” (STROBE) guidelines. Approval has been obtained from the Icelandic National Bioethics Committee, and the study is registered with Clinicaltrials.gov. The study will contribute to an improved understanding of the links between diet, gut microbiota and mental health in children through good quality study design by collecting information on multiple components, and a longitudinal approach. Furthermore, the study creates knowledge on possibilities for targeted and more personalized dietary and lifestyle interventions in subgroups.

**Trial registration numbers**: VSN-19-225 & NCT04330703.

## Introduction

### Mental disorders and intestinal permeability

It has been estimated that up to 20% of children and adolescents worldwide experience mental disorders [1]. Symptoms from the gastrointestinal (GI) tract are common among children with mental disorders [2–4]. Inherent to the rationale of a gastrointestinal role in mental disorders, including imbalanced microbiota, is the idea of intestinal permeability (IP) of the intestinal epithelial barrier. Imbalanced microbiota can result in dysbiosis, which, if left untreated, can affect the intestinal epithelial paracellular pathway [5]. Increased IP allows food-borne chemicals, including toxins, and microbial components, to enter tissues beneath the intestinal lining, which can result in local and systemic inflammation caused by pro-inflammatory cytokines in the intestine as well as outside the intestinal tract [6]. Loss of intestinal barrier function may lead to neuroinflammation and neuroimmune disorders such as autism spectrum disorder (ASD) [1, 4, 7], chronic fatigue syndrome [8], major depressive disorders (MDDs) [9, 10], and schizophrenia [11, 12].

Zonulin, a family of structurally and functionally related proteins, is currently the only known physiologic modulator of intercellular tight junctions and affects mechanisms that regulate the intestinal epithelial paracellular pathway. Zonulin upregulation has been associated with several chronic inflammatory diseases, low-grade inflammation, and autoimmune diseases, including ASD and attention deficit hyperactivity disorder (ADHD), which might have an autoimmune component [1, 13]. There is growing evidence, in genetically susceptible individuals, on changes in the intestinal microbiome composition and function, i.e., intestinal dysbiosis, possibly causing functional changes in intestinal permeability (IP). Functional changes in IP may lead to increased IP, contributing to increased antigen trafficking and break of tolerance, increasing the probability of developing a chronic inflammatory disease [6, 14, 15].

Intestinal microbiota-derived antigen and endotoxin trafficking from the lumen to the lamina propria has been found to trigger innate-and immunoregulatory responses, which may cause a pro-inflammatory micro milieu. Over time, an adaptive immune response could be mounted, producing pro-inflammatory cytokines, which may cause further opening of the paracellular pathway for the passage of antigens. The specific host genetic background has been found to affect where the inflammatory process will be targeted, i.e., in which organ or tissue [6, 13, 14, 16–18]. Dysbiosis and the presence of inflammation, as well as neuroinflammation, have all been described in mental disorders [13, 19].

The gut-brain axis involves bidirectional communication between the central and the enteric nervous system [20]. Increased IP might affect the enteric nervous system, impacting both mood and behavior [12]. The emerging recognition of the relationship between the gut-brain axis and the neuro-immune system provides a novel approach for potentially better understanding and managing mental disorders. There is an urgent need to investigate these emerging interrelations further.

### Mental disorders in children

The etiology of most mental disorders is unknown, but both genetic and environmental factors seem to play a role [21, 22]. Many mental disorders become visible during childhood and pose a challenge both to the children and their families, affecting everyday life and wellbeing. Research shows that up to 20% of children and adolescents may experience behavioral, mental, and neurodevelopmental disorders, including 10% with clinical diagnosis, resulting in disability in young people worldwide [23–25]. The most common mental disorders are ADHD, anxiety disorders, ASD, eating disorders, depressive disorders, disruptive disorders, tic disorders (TD) [26], and comorbidities are common. In the Diagnostic and Statistical Manual of Mental Disorders, 5th edition (DSM-V), neurodevelopmental disorders (ND) include ADHD, ASD, and TD. These disorders should be viewed as a spectrum rather than distinct disorders due to shared symptoms, genetics, and neuropathology [23, 27].

Recent studies that follow children from birth to adulthood indicate that most adult mental health disorders begin its origin in early childhood and adolescence [28, 29]. Despite evidence suggesting that overdiagnosis and overtreatment might exist to some extent, rates of diagnoses have increased substantially. A growing number of children and adolescents are now requiring treatments, including many types of interventions. In a systematic review of the literature that included 41 studies conducted in 27 countries from every world region [30], worldwide pooled prevalence of mental disorders was 13.4% (CI 95% 11.3–15.9). The most common diagnoses were: any anxiety disorder 6.5% (CI 95% 4.7–9.1), any depressive disorder 2.6% (CI 95% 1.7–3.9), ADHD 3.4% (CI 95% 2.6–4.5), and any disruptive disorder 5.7% (CI 95% 4.0–8.1). In comparison to the prevalence of other childhood chronic health conditions, such as obesity (16.8%) [31] and asthma (8.5%) [32], the high frequency of mental disorders and their associated negative consequences, render them major health priorities [30]. The burden of mental disorders among children aged 5–14 years has been studied in each of the six regions of the World Health Organization. Disability-adjusted life-years (DALYs) are the main indicator and are built from years of life lost (YLLs) and years of life lived with disability (YLDs). These studies showed that mental disorders in children are among the leading causes of YLDs and of DALYs in Europe and America [33].

A similar pattern is seen in Iceland at the outpatient Child and Adolescent Psychiatric Department (BUGL), where more than half of the children seen for the first time each year (*n≈*150) are diagnosed with ADHD, over 40% with anxiety disorders, over 30% with depressive disorders or disruptive disorders, and up to 25% with behavioral disorders or ASD, where overlapping of disorders is common [34, 35]. However, as mental disorders are thought to be products of multiple interacting causal factors rather than a single cause and are therefore multidimensional, mental disorders should preferably be evaluated dimensionally instead of categorically [36]. This has been introduced into the most recent Diagnostic and Statistical Manual of Mental Disorders (DSM-5), with more latitude to selecting severity of symptoms instead of a strictly categorical model where a disorder is either present or absent. In a research context, this approach is also considered more useful [37], especially as studies indicate that similar symptoms can have very different genetic origins [38, 39]. Clinical guidelines usually do not recommend medication as the first line of treatment for mental disorders except in severe cases [40]. Indeed, medication can result in many unwanted side effects. Other standard therapeutic options are psychological treatments [41, 42] depending upon the service available at each location. However, it is urgent to consider also other aspects. For example, symptoms from the GI tract are common among children with mental disorders [2–4], and there are indications that these have a higher prevalence of atopic reactions [43–45]. Research shows that childhood ADHD is associated with atopic diseases and impetigo [44]. Atopic diseases seem to be associated with ADHD symptoms severity in children and adults [46]. However, there are possible limitations inherent to observational studies and further research is needed. It is necessary to study the underlying mechanisms as well as to evaluate preventative, diagnostic and therapeutic interventions.

### Diet, intestinal microbiota, and mental disorders

In recent years, the association between diet, nutritional status, and the intestinal microbiota [47–49] has become a focus of interest, not least concerning mental health disorders [50–56]. The microbiota in children is affected by dietary habits and influences nutritional status. There is a link between the gut microbiota and malnutrition in children, as alteration in microbiota of severe acute malnourished children exhibits lower relative diversity when compared to healthy children. Moreover, the microbiota does include decreased levels of *Bacteroides* and increased levels of *Proteobacteria* in malnourished children [57]. The gut microbiota has been associated with obesity, a multifactorial chronic disorder, as is associated with other metabolic disorders and the gut microbiota is considered one of environmental regulators [58]. Several human and animal studies have revealed increased number of *Firmicutes* versus decreased number of *Bacteroidetes* in obesity [59–61]. Growth stimulation of the generally considered beneficial bacteria of Bifidobacterium and Lactobacillus by nutritional strategies with fiber or prebiotics may impact gastrointestinal health [62]. The microbiota can thus be affected by both pre- and probiotics [63–66] while dietary factors have been associated with both mental health and preexisting, existing, or other GI health problems [4, 67–69]. Furthermore, studies have indicated the importance of a healthy diet, i.e., healthy diet reflecting consumption of salads, fruit, fresh vegetables, and fish and the effects of whole-of-diet interventions rather than examining only individual foods/nutrients, as a potential factor in the treatment of anxiety [20], depression [70–72], and ADHD [73, 74]. In addition, single nutrients, e.g., optimal intake of vitamin D, omega-3 fatty acids [75–78] and iron and low exposure to heavy metals show positive outcome [79]. However, vitamin D, iron and low exposure to heavy metals did neither improve anxiety or depression except for omega-3 fatty acids which improved anxiety [78].

Studies have provided substantiated evidence in support of docosahexanoic acid (DHA), an omega-3 fatty acid, being a beneficial bioactive compound for brain function but it’s possible effects on depression disorders are still unclear [80]. Preliminary data point towards beneficial effects of omega-3 fatty acids on pediatric depression [81–86]. However, sufficient evidence is lacking to support/rule out that omega-3 fatty acids are potential treatments for depression as large-scale studies are needed to validate these results.

It is well known that eating is an integral part of the behavioral challenges in many mental disorders, with monotonic food choices and food aversions being common, which in turns affects the microbiota [87, 88]. The intestinal microbiota among children with disorders such as ASD and ADHD has been found to have a different composition compared to both community controls and healthy full siblings [89–93] living in the same household. The studies reveal a significant increase in the Bacteroidetes/Firmicutes ratio and *Clostridium* levels in children diagnosed with ASD and reduced *Bifidobacterium* levels in children diagnosed with ASD or ADHD. However, these studies often include few participants as well as being methodologically heterogeneous, making it hard to generalize the results [94–96].

The symbiotic relationship with the microbiota has evolved, and studies indicate that the host’s genetic composition might be related to host-microbiota composition [97]. Research has shown that the intestinal microbiota might influence the host genomic organization and gene regulation, i.e., gene expression in the gastrointestinal tract, and the mechanisms of gene regulation in cells of the immune system [98]. Cell components from the microbiota including their metabolites seem to be involved in the transcriptional response of the host to microbial colonization [99, 100]. Research shows that the intestinal microbiome may remodel host chromatin, cause differential splicing, directly interrupt host signaling cascades, and alter epigenetic landscape [101]. However, mechanistic understanding of this relationship is still in its infancy, although the phenomenology of the cross-regulation of gene expression between the intestinal microbiota and the cells of the immune system has been established [102]. Host genetics may differentially influence distinct members of the microbiota. Research has shown that abundances of certain taxa is different between monozygotic twin pairs when compared with dizygotic twin pairs [98].

Furthermore, genome-wide association studies have identified numerous single-nucleotide polymorphisms (SNPs) associated with mental disorders [103], which can be used to calculate individual polygenic risk scores for study participants. However, these SNPs are associations and mechanisms are still unknown.

Microbial imbalance, i.e., intestinal dysbiosis can be defined as qualitative and quantitative changes in the intestinal microbiota, the local distribution, and metabolic activity [5]. Dysbiosis has long been implicated in the development or exacerbation of mental disorders [104]. It has been suggested that the intestinal microbiota and the brain are linked in a bidirectional relation, i.e., the microbiome–gut–brain axis [105]. The advances in research and in understanding of the role of the microbiome in neurodevelopment and mental disorder have been remarkable in the last few years. Influences of the microbiome and how it might contribute to dysregulation of brain function is an area of growing interest [52, 106–110]. Diet-induced dysbiosis substantially influences brain function through shaping the intestinal microbiome [104, 105, 111].

Studies have also established a potential link between salivary microbiome alterations and disease initiation [112–114]. Wingfield et al. [113] revealed that the composition of the oral microbiome is associated with depression in young adults and Quing et al. [114] provided hypothesis of how the oral microbiota could influence schizophrenia. Differences in alpha and beta diversity of the salivary microbiome have been observed in both these studies, with clear separation into distinct clusters between cases and healthy controls [113, 114]. More research is needed on the oral-brain axis to clarify the biological links and interconnections between the oral microbiome and the pathophysiology of mental disorders.

Unhealthy dietary pattern may increase the risk of developing depression or anxiety, whereas a healthy dietary pattern may decrease it [105]. Diet is one of the most significant factors that influences the human intestinal microbiota structure and function, and the association found between diet and mental health might partially be through the microbiota. An adequate supply of micronutrients and macronutrients is essential to well-being and provides the foundation for microbiome health, low inflammation as well as for the efficacy of other psychotherapeutic and psychopharmacological interventions [115, 116].

Dietary effects on the gut microbiome are evident, even as early as infancy. Intestinal microbiome differences have been observed between breast-fed infants with a greater prevalence of Bifidobacteria compared to formula-fed infants [117]. Existing human studies of depression and intestinal microbiota report depression-specific findings regarding proportions of microbiota [56, 118–120]. Moreover, research shows an enrichment of pro-inflammatory bacteria as well as a depletion of specific anti-inflammatory butyrate-producing bacteria in subjects diagnoses with anxiety, bipolar disorder, depression, and schizophrenia [121].

There is growing evidence on changes in the intestinal microbiota composition and function, i.e., intestinal dysbiosis, which may cause functional changes in intestinal permeability (IP) in genetically susceptible individuals. Functional changes in IP may lead to increased IP, which could contribute to increased antigen trafficking and break of tolerance, and therefore, increasing the probability of developing a chronic inflammatory disease [6, 14, 15].

Loss of intestinal barrier function may lead to subsequent increased serum levels of microbiota-derived molecules and, in turn, activation of the immune system, which may lead to neuroinflammation. This has been described in several neuroimmune disorders such as ASD [1, 4, 7], chronic fatigue syndrome [8], major depressive disorders (MDDs) [9, 10], and schizophrenia [11, 12].

It is vital to study the intestinal microbiota and IP further regarding diet and mental health [56]. It is important to overcome previous limitations and increase the number of subjects, coordinate strategies, and assess confounding factors, e.g., the severity of the mental disorders and problems from the GI tract, and secure quality collection [94, 122] as well as lifelong medication use. Biosamples will be collected and analyzed with the latest technology factors in addition to the microbiota, that can shed a better light on research questions and potential mechanisms. As data on the gut-brain axis demonstrates association between intestinal microbiota composition and mental disorders such as depression, we will collect fecal samples within this study for microbiome analysis. However, longitudinal studies are lacking, and therefore in this present study, collection of data will be repeated in three years. These are the basis of the current study on Meals, Microbiota and Mental Health in Children and Adolescents, i.e., the MMM study.

Our hypothesis for the current study is the following; There are differences between cases and controls regarding dietary intake, nutritional status and/or the intestinal microbiota and related metabolic factors, in physical symptoms from the digestive tract and in intestinal permeability. In addition, we hypothesize that there are differences in other potentially relevant background factors and therefore comparisons with full siblings will give insight into family variability.

### Aim

The aim of this observational longitudinal case-control study is to compare diet, intestinal permeability, intestinal microbiota, and related metabolic factors in children and adolescents diagnosed with mental disorders and control groups to identify potential patterns that may contribute to the symptoms.

## Methods

### Study type and design

The MMM study is a double-blinded observational longitudinal case-control study (Fig 1). Adherence to the Strengthening the Reporting of Observational Studies in Epidemiology (STROBE) guidelines was pursued throughout the study design.

**Fig 1 pone.0273855.g001:**
[figure not shown]
Meals, Microbiota, and Mental Health of Children and Adolescents study design.

#### Study population and participants, recruitment, and sample size

All children and adolescents between 5 to 15 years of age referred to the outpatient clinic of the Child and Adolescent Psychiatry Department (BUGL) over one year, will be invited to participate (*n≈*150). There are two control groups, i.e., age and sex-matched children from the same postal area (n*≈150)* and full siblings (same parent siblings, i.e., brothers and sisters) living in the same household and close in age (+/- 3 years; n<150).

#### Study group

Interested patients of the Child and Adolescent Psychiatry Department (BUGL) at The National University Hospital in Reykjavik the guardians and child will receive invitation letters with information about the MMM-study. In a follow-up phone call questions about the study can be answered and more information given. If interested to participate, an informed consent is signed, including a letter to the child’s teacher allowing the researcher to contact the teacher. For the healthy control groups (group I and II), a randomly selected child (matched by gender and age and within the same zip-code) will be contacted by the Social Sciences Research Institute (SSRI) and invited to participate similarly (control group I). Parents will be asked if a potential full sibling (+/-3 years) living in the same household could be included in the study (control group II) as we hypothesize that there are differences in other potentially relevant background factors comparisons with full siblings, and therefore, this will give insight into family variability. However, this is *not* a prerequisite for participation.

A kit including tools for collecting biosamples with good instructions and a booklet for the three-day dietary recording will be provided. In addition, links will be sent for demonstrating the specimen collection, however medical auxiliary will be available for assistance by request. Participants will be asked to be present for a blood test at the Landspitali-University Hospital in Reykjavik or Akureyri-Hospital, in Iceland, based on their residency. Eligibility criteria for the study and control groups are outlined in Table 1.

**Table 1 pone.0273855.t001:** Eligibility criteria for the MMM study.

Participant type	Inclusion criteria	Exclusion criteria
Cases	Children and adolescents 5–15 years, males, and females, referred for their first visit to the outpatient clinic at the Child and Adolescent Psychiatry Department (BUGL). Living in Reykjavik or Akureyri or surroundings.	Not speaking/understanding Icelandic language Recent use of antibiotics (within last 4 weeks)
Control group I: *Healthy controls*	Children and adolescents 5–15 years not diagnosed with mental disorders. Living in Reykjavik or Akureyri or surroundings.	Mental disorder diagnosis Recent use of antibiotics (within last 4 weeks)
Control group II: *Parental siblings (full siblings*, *i*.*e*., *brothers and sisters)*	Full siblings living in the same household close in age to the study subjects (+3y) not diagnosed with mental disorders. Living in Reykjavik or Akureyri or surroundings.	Mental disorder diagnosis Recent use of antibiotics (within last 4 weeks)

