### Sample collection

All biosamples, except blood, will be collected at home by the participants, with help from their guardians when needed. A biosample kit will be delivered to the participants and collected by research staff to make sure the samples will be in good condition and usable. Participants are asked to collect the biosamples preferably towards the end of the 3-day food registration within the first month into the study and store the biosamples in a specific container in a cool dry place (4–8°C) according to the manufacture’s guidelines. Commercial kits from DNA Genotek´s microbiome stool collection kits are used to collect and optimally stabilize stool samples. Fecal and saliva samples will be collected for microbiome 16s rRNA amplicon sequencing. A buccal swab will be collected for whole-genome genotyping of human DNA. Urine samples will be collected for targeted analysis of food-related peptides and untargeted metabolomics profiling. Blood will be collected either at Landspitali, University Hospital in Reykjavik, or Akureyri Hospital in Akureyri, depending on residence, for analyzing serum zonulin, inflammatory biomarkers, e.g., CRP, interleukins, and nutritional status, i.e., hemoglobin, ferritin, folic acid, Vitamin B_12_, 25-hydroxy-vitamin-D, and fatty acids. The biosamples are preferable to be collected towards the end of the 3-day food registration according to standard procedure as mentioned above. The kit is then collected from both cases and controls by the researchers along with the food diary in Reykjavik, Akureyri, and near surroundings. Participants will be able to deliver the samples to a provided location if they prefer. For other locations in Iceland, the samples will be sent out, including guidelines on how to resend them to the researchers after their collection. The urine samples will be aliquoted into smaller tubes for storing at a laboratory unit at the University Hospital or Akureyri Hospital in a -80°C freezer along with the other biological samples.

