#### Integrative analysis of Meals, Microbiota, and Mental Health data

For each type of omics- and biomarker data (nutrients, microbiota, metabolomics, food-related peptides, inflammatory factors), appropriate preprocessing, and quality control will be coordinated and performed by the researchers. All data will be appropriately normalized and transformed, checked for potential batch effects and outliers removed. The effects of potential confounders such as age, sex, body mass index, ROME IV (for intestinal microbiota), medication, or diet will be investigated. For each datatype cases will be compared to the two control groups, but also associations between the different variables will be looked for separately, as well as in relation to sub-groups, using multivariate models including adjustments for confounder variables. Using analysis of covariance (ANCOVA) the influence of potential confounders such as age, sex, body mass index, ROME IV (for intestinal microbiota), medication and diet will be investigated. Benjamin-Hochberg false discovery rate will be applied, correcting for multiple hypothesis testing.

Integrating different types of high-dimensional omics data is a challenging task, and multiple approaches can be undertaken. A computational framework for such analysis [163] has been suggested based on dimensionality reduction of omics data using co-abundance clustering, followed by cross-omics correlation analysis focused on features that differ between cases and controls. In addition, other types of omics integration approaches will be applied, as recently reviewed [164, 165], such as robust sparse canonical correlation, co-inertia, or Procrustes analysis, to identify shared patterns across omics and dietary data in the context of mental health.

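### Community controls are not matched on calendar time and season is not a named confounder, so seasonal outcomes carry avoidable variance and, if sampling calendars differ, bias

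*Protocol article*

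**What the plan says.** All places are in the protocol article.

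- **Matching.** Under Study group, for control group I, "a randomly selected child (matched by gender and age and within the same zip-code) will be contacted by the Social Sciences Research Institute (SSRI". The Study population section describes "age and sex-matched children from the same postal area"; the Abstract has only "sex-matched children from the same postal area". None of the three mentions calendar time.
- **Case accrual.** Children are "referred to the outpatient clinic of the Child and Adolescent Psychiatry Department (BUGL) over one year, will be invited to participate". That one-year period is stated for cases. No calendar period is stated for group I.
- **Timing of samples.** Under Sample collection, the home kit is used "preferably towards the end of the 3-day food registration within the first month into the study", which is each participant's own clock. Blood is drawn at one of two hospitals. Neither is tied to the date of the matched case.
- **Seasonal outcomes.** The blood panel includes "25-hydroxy-vitamin-D, and fatty acids". A three-day food diary is also kept, and the hypothesis at the end of the Introduction names dietary intake and nutritional status.
- **Adjustment.** The Integrative analysis section gives its list twice: "The effects of potential confounders such as age, sex, body mass index, ROME IV (for intestinal microbiota), medication, or diet will be investigated", and again for the ANCOVA, "the influence of potential confounders such as age, sex, body mass index, ROME IV (for intestinal microbiota), medication and diet will be investigated". Season and sampling date appear in neither.

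**The concern.** Cases enter through clinic referral, and group I enters through a separate institute. The plan does not make the two sets of sampling dates cover the year in the same way, and no named covariate would correct for a difference.

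Two consequences follow for outcomes that vary with season:

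1. Seasonal variation stays in the residual and costs precision, even when the two groups' calendars are identical.
2. If the calendars differ, part of the seasonal swing appears as a difference between cases and group I. The planned false discovery rate correction deals with multiplicity and does not remove a confounding bias.

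Diet as a covariate helps only in part. It may absorb some seasonal effect in microbiota or metabolites. It cannot do so when diet is itself the outcome, nor for vitamin D that does not come from food.

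**Working it through.** **The plan's own figure.** The plan gives no figure on season. Its only calculation is 62 per arm, for 30% versus 10% with α 0.05 and 80% power. The two-sided pooled formula gives [1.96·√(2·0.2·0.8) + 0.842·√(0.3·0.7 + 0.1·0.9)]² / 0.2² = (1.109 + 0.461)² / 0.04 = 61.6, so 62. It reproduces, and this point does not change it. The target of 100 per arm is used below.

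**Assumptions (not in the documents).** The outcome follows A·cos(2πt/12), with t in months and A in units of the within-season SD. A is taken as 0.2, 0.4 and 0.6. There is no true group difference, the test is a two-sided z test at 0.05, and season is not adjusted for. Each group's SD is taken as √(1 + A²/2), a full-year approximation.

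**Loss of precision when calendars are equal.** With sampling spread over the year, season adds A²/2 to a within-season variance of 1.

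| A | added variance A²/2 | share of total, (A²/2)/(1 + A²/2) |
|---|---|---|
| 0.2 | 0.02 | 2.0% |
| 0.4 | 0.08 | 7.4% |
| 0.6 | 0.18 | 15.3% |

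If the two terms describe season fully, 100 adjusted children per arm are worth about 102, 108 or 118 unadjusted ones.

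**Bias when calendars differ.** The mean of the cosine over a window of W months is s(W) times the cosine at the window's midpoint, with s(W) = sin(πW/12)/(πW/12). So s(12) = 0, s(9) = 0.707/2.356 = 0.30 in absolute value, and s(6) = 1/1.571 = 0.64.

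| Sampling calendars | bias | A = 0.2 / 0.4 / 0.6 (SD) | false-positive rate |
|---|---|---|---|
| Both even over 12 months, controls 3 months later | 0 | 0 / 0 / 0 | 5% |
| Both over 9 months (peak missed by cases), controls 1 month later | 0.04A | 0.01 / 0.02 / 0.02 | 5% |
| Cases over 9 months (peak missed), controls over 12 | 0.30A | 0.06 / 0.12 / 0.18 | 7% / 13% / 22% |
| Cases over 12 months, controls all in the peak half-year | 0.64A | 0.13 / 0.25 / 0.38 | 15% / 41% / 70% |

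One rate in full, for row three with A = 0.4: the standard error is √1.08·√(2/100) = 0.147 and the bias divided by it is 0.12/0.147 = 0.82. The rejection rate is 1 − Φ(1.96 − 0.82) + Φ(−1.96 − 0.82) = 0.13.

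For equal windows with a lag of L months, the shift at the worst phase is A·s(W)·2·sin(πL/12). At W = 9 this is 0.30A for L = 2 and 0.42A for L = 3. At W = 12 it is 0 for any lag.

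For scale, 100 per arm detects (1.96 + 0.842)·√(2/100) = 0.40 SD with 80% power.

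**The case against.** The strongest reply is that the one accrual window the article states is a full year. If both groups are spread evenly over it, the bias is exactly zero at any constant lag. A larger shift needs a shorter window or different calendars, and no section states either. This stands: the bias is a risk, not a stated error. Even accrual is nevertheless not secured. The one-year period is given for cases only, and the Data collection section foresees delayed recruitment and leaves the response to the advisory board.

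The second reply is that an article condenses its protocol and that the confounder list is introduced as examples. This stands in part: season is unnamed, not excluded, and an analysis plan may add it. But matching is a design feature that the article does state and counts as a strength in Table 3, and a later covariate cannot restore calendar overlap once sampling is done.

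A reader might infer four stronger points that the document does not support:

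- *That siblings share the case's season.* They live in the same household and are recruited through the parents, but no joint sampling date is set.
- *That a seasonal difference seen only against group I would be read as a family effect.* The plan says only that siblings give insight into family variability.
- *That every comparison is affected.* Nothing in the document supports this for genotype, the rating scales or zonulin.
- *That the follow-up wave needs its own calendar rule.* An interval of three whole years already returns each child to roughly the same season.

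**Conclusion.** The point holds in a limited form. For 25-hydroxy-vitamin D and dietary intake, and possibly for diet-related microbiota and metabolites, season is controlled neither by the stated matching nor by any named covariate.

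The loss of precision does not depend on unequal calendars. It is about 2% to 15% of total variance for the assumed amplitudes.

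The bias in cases versus group I is conditional. It is nil under even 12-month sampling of both groups and negligible when the calendars nearly coincide. It is 0.06 to 0.18 SD if cases miss a three-month peak that controls cover, and larger only under strongly unequal calendars. The amplitude, lag and calendars are all assumptions, so none of these figures should be read as the bias expected in this study. The point does not touch the sample size, and it is a low-cost improvement, not a flaw that undermines the design.

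**What to change.** 1. Record the calendar date of each collection (diary, home kit, blood draw). The article does not say that these dates are kept.
2. Name sampling month, as one sine and one cosine term, in the ANCOVA and multivariate models for dietary, vitamin D, microbiota and metabolite outcomes.
3. Ask the recruiting institute to aim at sampling each group I control close in calendar time to its index case. This should be a target and not an exclusion rule: Table 3 gives willingness to participate as the main limitation, and a hard window could lose controls.
4. Report the distribution of sampling months by group, so that a reader can see whether the calendars overlapped.

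The cost is two degrees of freedom per model, a date field, one instruction to the recruiting institute and slightly less scheduling flexibility. The model terms correct well only where the calendars overlap, which is why the target in step 3 is worth having as well.
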